# Home‐based high‐intensity interval training for people with Parkinson's: Protocol for the HIIT‐Home4Parkinson's randomized, controlled feasibility study

**DOI:** 10.1002/hsr2.1800

**Published:** 2024-01-07

**Keywords:** exercise, HIIT, Parkinson's disease, rehabilitation, home‐based

## Abstract

**Background:**

High‐intensity interval training (HIIT) is feasible and beneficial for some people with Parkinson's (PwP), although adherence to extended programs may be problematic. PwP face barriers to exercise such as lack of time, expense, and difficulty with travel logistics due to motor symptoms. HIIT based in the home setting if practical, could therefore be apposite for PwP by overcoming these barriers. However, until now, no home‐based HIIT program for PwP has been developed. Cocreated by PwP, clinicians, and family members, the HIIT‐Home4Parkinson's (HH4P) program is an innovative, 12‐week home‐based HIIT program for PwP. This protocol describes a feasibility study designed to assess the feasibility and safety of the HH4P program, explore outcomes that may be sensitive to change, and inform the implementation of a potential full trial.

**Methods/design:**

Using a randomized controlled parallel group design, 24 independently mobile people with Parkinson's of mild to moderate disease severity will be randomized 1:1 to either the HH4P program plus usual care, or usual care alone. Both groups will be assessed at baseline, and upon the completion of the program. Outcomes will include feasibility and safety factors such as recruitment, completion, adverse events, and intervention fidelity with qualitative evaluation along with mechanistic, physiological, and clinical outcomes.

**Discussion:**

Results of this study will inform the rationale and methodological considerations for a full trial with long‐term follow‐up. Ultimately, further establishing the practicality and utility of home‐based HIIT could provide an important exercise option for PwP, potentially leading to extended participation and increased health and well‐being for this population.

## BACKGROUND

1

Affecting 6.1 million people globally,^1^ Parkinson's disease (Parkinson's) is a neurodegenerative disorder characterized by motor impairments such as bradykinesia, postural instability, and rigidity along with a range of nonmotor symptoms.^2^ People with Parkinson's (PwP) can also demonstrate reduced aerobic fitness,^3^ potentially leading to additional health and well‐being complications. High‐intensity interval training (HIIT) is a common form of exercise, consisting of alternating bouts of high‐intensity exercise and periods of rest or active recovery. HIIT has been found to be feasible and safe for some PwP and can improve cardiorespiratory fitness, motor symptoms, and levels of brain‐derived neurotrophic factor (BDNF),^4^ evinced to have neuroprotective qualities.^5^ In addition, HIIT for PwP has been found to be at least as beneficial as moderate‐intensity continuous exercise, with reduced volume and time commitment,^4^ as reflected in other clinical and healthy populations.^6^, ^7^, ^8^ However, despite these benefits, PwP may not adhere to extended HIIT programs.^4^ PwP face restricting factors such as expense, concerns of exercising in a group setting, travel logistics due to motor symptoms,^9^ and lack of time.^10^ HIIT based in the home setting would appear to be a potential way to overcome these barriers, and possibly facilitate initial engagement and extended participation. However, until now, no home‐based HIIT program has been developed for PwP; therefore, the practicality and utility of home‐based HIIT remain unknown.

“HIIT‐Home4Parkinsons” (HH4P) is a novel, patient‐focused, cocreated home‐based HIIT program for PwP. HH4P will be delivered as an adaptable, individualized, 12‐week home‐based HIIT intervention, structured to maximize achievability through remote supervision and the use of appropriate physical and online resources. As previously described,^11^ the development of HH4P was based on the Medical Research Council (MRC) framework for the development and evaluation of complex interventions,^12^, ^13^, ^14^ continually informed by input from patient and public involvement (PPI) contributors and clinicians within a cocreative, iterative planning process of online focus groups and exercise testing. Having now optimally developed the HH4P program, it is critical to undertake a feasibility study before undertaking a definitive trial to address remaining uncertainties. This protocol describes the HH4P parallel‐group randomized controlled feasibility study, developed to evaluate the practicality and utility of the HH4P program, and ultimately inform the development of a full trial designed to facilitate the initial engagement and extended participation in HIIT for PwP.

This feasibility study has three aims.
1.To evaluate the feasibility, safety, and acceptability of a 12‐week home‐based HIIT program for PwP.2.To identify the clinical and physiological outcomes that could be feasible and sensitive to change compared to usual care in a full home‐based HIIT trial for PwP.3.To elucidate the key methodological considerations for the implementation of a full home‐based HIIT trial. Table 1 shows specific objectives relating to each aim.

**Table 1 hsr21800-tbl-0001:** Feasibility study objectives.

Aim	Objectives. Aims will be achieved by determining
A	i. HH4P program safety ii. Adherence to the HH4P exercise program iii. Completion of the HH4P exercise program iv. Achieved exercise intensity v. Acceptance of HH4P exercise program and delivery procedures vi. Practicality of intervention resources vii. Intervention fidelity
B	i. Responsiveness to change in mechanistic, physiological, and clinical outcomes to inform the selection of primary and secondary outcomes for a definitive trial ii. Feasibility of outcome measure procedures (including rates of outcome measure completion) iii. The association between baseline and postintervention scores
C	i. Suitability and feasibility of eligibility criteria ii. Numbers of eligible participants from the target population iii. Willingness of patients to be randomized iv. Baseline factors most strongly associated with outcomes, to inform potential stratification in a full trial v. Recruitment/retention rates and suitability of procedures vi. Sample size calculation required for a fully powered randomized controlled trial vii. Resources required for a full trial

### Registration

1.1

The HH4P randomized, controlled feasibility study was registered in clinicaltrials.gov, identification number NCT05485428.

## METHODS/MATERIALS

2

This protocol was written in accordance with the SPIRIT 2013 checklist; recommended items to address in a clinical trial protocol and related documents,^15^ and the CONSORT 2010 statement: extension to randomized pilot and feasibility trials^16^ (see Supporting Information).

### Study design overview

2.1

This is a randomized controlled parallel group feasibility study with mechanistic, physiological, and clinical subcomponents. Twenty‐four PwP will be randomized in a 1:1 ratio either to the HH4P 12‐week, home‐based HIIT program plus usual care (intervention) or to usual care alone (control). Assessments will include feasibility and safety factors, and pre and postintervention assessments of potential primary and secondary outcomes undertaken by assessors blinded to group allocation. Both groups will undergo objective physical activity (PA) monitoring 1 week before, and in Week 7 of the intervention. Exercise participants will be invited to attend a posttrial focus group constituting a qualitative addition to assessment of intervention fidelity.

### Roles and responsibilities

2.2

Research team:

The chief investigator (CI; author [name]) has overall responsibility for the implementation of this trial. The CI has lead responsibility for writing ethics submissions, developing training materials, and recruitment, and will be supported by three members of the supervisory team (ST; authors [name], [name], and [name]). The CI is also responsible for data analysis, participant liaison, online resources, and materials. One member of the ST ([name]) will be allocated to undertake postrandomization outcome assessments, blinded to trial arm allocation. Another member of the ST ([name]) who will not be involved in assessments will undertake randomization procedures.
Trial steering committee

This study will be overseen by an independent trial steering committee (TSC). The TSC will consist of one service user (PwP), and a practicing clinician. The TSC will provide ongoing guidance and advice on any conflict that arises within the research team. The TSC will receive three progress reports delivered by the CI throughout the course of the study.

### Setting

2.3

The HH4P program is based at the University of Plymouth (UoP), Devon, UK. All research assessments are currently scheduled to take place in the Exercise, Nutrition and Health Laboratory, Link Building, UoP. All HIIT sessions will take place in participant homes, expected to be located in the Southwest of England.

### Participants

2.4

Participant eligibility criteria will include having Parkinson's with mild to moderate disease severity (Hoehn and Yahr Stages 1–3). This criterion was applied as a recent systematic review^4^ concluded there was insufficient evidence to suggest HIIT as a suitable exercise option for those of greater functional disability. An upper age limit will not be applied, as eligibility emphasis will be on appropriate functional and cognitive ability (Table 2).

**Table 2 hsr21800-tbl-0002:** Participant eligibility criteria.

Inclusion criteria	Diagnosed with Parkinson's disease Aged 18 years or older (no upper limit) Hoehn and Yahr Stages 1–3 (mild to moderate disease severity) Capacity to consent under the Mental Capacity Act 2005, and sufficient cognitive ability to follow an exercise program Based at home with space to perform an exercise program (approximately 2 m^2^) Willing and able to travel to intervention assessments Access to a computer, Smart Phone, or tablet and to the internet
Exclusion criteria	Other concurrent neurological conditions Comorbidities that would prevent/be exacerbated by high‐intensity exercise such as forms of cardiovascular disease Advised to not participate following medical consultation Participation in a contemporaneous interventional study

### Sample size

2.5

As this is a feasibility study, an a priori power calculation to detect a significant between‐group difference in a primary outcome is not appropriate.^17^ Instead, this study aims to gain estimates of the likely rates of recruitment and retention, and variability of the proposed primary and secondary outcomes to inform sample size calculations for a potential full trial (objective Cvi). For this feasibility study, we aim to recruit 24 participants^18^ (12 interventions and 12 usual care controls). It is anticipated that to recruit these 24 participants we will need to telephone screen approximately 37 people, of which approximately 35% (*n* = 13) will be found to be ineligible after screening, leaving 24 people to grant consent, and ultimately be randomized. From other similar studies,^19^ we believe that retention rates will be at least 85%, leaving a likely sample at the final follow‐up of between 20 and 24 participants.

### Recruitment strategy

2.6

This feasibility study will aim to recruit from the Southwest of England over a 3‐month period, but participants from other regions are eligible if they are willing/able to travel to the UoP for assessments.

Participants will be identified through the following sources:
1.University Hospitals Plymouth National Health Service Trust Parkinson's Service (clinicians will pass on promotional materials during scheduled appointments)2.Livewell Southwest (as above)3.Parkinson's UK (promotional material will be emailed to members)4.University of Plymouth social media outlets

All promotional materials will include information inviting people to email expressions of interest to the CI. Upon receipt of interest, potential participants will be directed to a Jisc online participant information sheet (PIS), including estimated start and completion dates and a short questionnaire. Participants will complete personal and telephone contact details and a statement of permission to undertake telephone screening.

### Screening process

2.7

The CI will telephone potential participants to answer any further questions and to screen for eligibility using a preformatted screening checklist based on the eligibility criteria. Once eligibility is established, an appointment letter for baseline assessments will be sent via email by the CI. This will include information that assessments will be undertaken in the “on” medication state, and to time medication accordingly. During the baseline assessment, eligibility will be confirmed in person, with signed consent, assessment of blood pressure (BP), and a bespoke health screening questionnaire completed.

### Recruitment rate

2.8

This feasibility study will help to elucidate the recruitment rate for the planned definitive trial as we will record the sources of recruitment for all participants in this study, and ensure that the distribution is considered when extrapolating likely recruitment rates for the main trial.

The recruitment period for this feasibility study is 3 months. The HH4P recruitment pathway can be seen in Figure 1.

**Figure 1 hsr21800-fig-0001:**
[figure not shown]
Recruitment pathway. CI, chief investigator; GP, general practitioner; NHS, National Health Service; PIS, participant information sheet; UoP, University of Plymouth.

### Consent

2.9

There will be three layers of consent to this study:
1.Permission to be screened:

PwP interested in participating will be invited to complete an online form which includes a statement of permission to undertake the telephone screening process.
2.Consent to be recruited to the feasibility study:

Written informed consent will be obtained by the CI at the baseline assessment session before any data collection. Having been previously provided with study information via Jisc online, participants will have had the opportunity to review the information sheet and ask any questions before attending the baseline assessment session. Consent will also be sought to contact patients' GP to inform them of participation in the trial.
3.Consent to participate in posttrial focus groups:

Participants will be informed of the postexercise program focus group within the PIS, and consent will be included within the prebaseline informed consent process.

### Assessment sessions and home visits

2.10

All participants will attend two assessment visits to the UoP. The first assessment visit will take place 1 week before the start of the intervention to collect baseline data and ascertain preintervention outcome scores. Participants will then be given preprogrammed PA monitors, to objectively measure PA for a period of 7 days. During this week, a blinded member of the ST ([name]) will randomly allocate the participant to either the HIIT or control group.

After this 7‐day period, the CI will undertake a home visit to collect PA monitors, provide HIIT participants with resources, inform participants of group allocation, and provide both groups with instruction (see [name] et al.^11^ for details). All participants will be reminded that allocation to either intervention or control arm of the trial was informed by chance and occurred after baseline assessment.

The second assessment visit to ascertain postintervention outcome scores will be 24 h after the completion of the program. Figure 2 shows a timeline of study events and assessments.

**Figure 2 hsr21800-fig-0002:**
[figure not shown]
Timeline of study events and assessments. HH4P, HIIT‐Home4Parkinson's; UoP, University of Plymouth.

### Outcomes

2.11

#### Baseline data

2.11.1

Baseline data will be collected at the initial assessment visit during which eligibility is confirmed and once informed consent is obtained/bespoke health screening questionnaire is completed. The initial assessment visit will take place 1 week before the start of the HH4P program delivery date. The following baseline data will be collected:
Demographic data: Gender, age, ethnicity, home circumstances (who they live with), and employment status (as indications of socioeconomic status).Anthropometric data: Body mass (kg), height (cm), and body mass index will be collected/calculated with validated protocols, using a calibrated stadiometer and digital scales.Lifestyle data: Smoking status.Diagnostic data: Hoehn and Yahr stage.^20^
Medications and comorbidities: All current prescribed medications and dosage will be listed and coded.Blood pressure: If BP results are abnormal according to clinical guidelines,^21^ the participant will rest for 10 min. BP will then be remeasured. If BP is still abnormal the participant will be asked to seek medical appraisal before reapplying for the study. Also, participants will be constantly visually monitored during assessment tests for changes in BP. Guidance on symptoms related to extreme rises or drops in BP will be included in the home exercise support documentation.

### Feasibility outcomes

2.12

Measures of adherence and engagement:
Program completion (Objective Aiii)

Program completion will be defined as the percentage of participants that completed the 12‐week program of exercise or usual care, from those that underwent initial randomization.

Attendance at online group sessions (Objective Aii)Frequency and duration of exercise sessions (Objective Aii)Web‐based participant heart rate (HR) monitoring (Objective Aii)

Engagement in the home‐based program (exercise choice, HIIT session frequency, and duration) will be monitored based on exercise diary data recorded by the participant over the 12‐week program. Adherence will also be monitored through continual observation of online HR data (see below) and through attendance at online group meetings.

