### Interventions

2.22

HH4P (HIIT + usual care).

The HH4P program is a 12‐week, thrice weekly HIIT program with the emphasis on providing options to facilitate individual preference, ability, and disease stage. As previously described in detail,^11^ HIIT sessions will comprise four sets of three 45 s bouts of high‐intensity exercise (≥75% HR_max_), with each bout interspersed with 15 s of rest. A 2‐min rest period will follow each set. HIIT sessions will last for 32 min each including warm‐up and cool‐down periods. Participants will choose from a range of exercises and will be supported by both physical and online resources.
Usual care control group

All participants allocated to this group will continue to receive their usual clinical care; thus, with the exception of the trial assessments they will not be asked to attend any additional visits or sessions.

Both the HIIT and control group will be asked to not begin additional structured physiotherapy or exercise sessions, or undertake contemporaneous interventional studies.

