### Progression to a full trial

2.32

A full trial application will be made if minimum success criteria are achieved in the key aims and objectives. These criteria will be finalized in discussions involving the CI, ST, and TSC and could include:
a minimum of 80% of consented participants randomized to the intervention group engaging with the 12‐week HH4P intervention.a minimum of 80% completion rate of key outcome measures (pre and post).

There are also other areas such as participant acceptability, and feasibility of study procedures that will be taken into consideration when deciding whether to progress to a full trial application.

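### Program completion (Objective Aiii) counts usual-care participants, so it does not measure completion of the HH4P exercise program

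*Protocol article*

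**What the plan says.** Table 1 (Background) lists Objective Aiii as "Completion of the HH4P exercise program". Section 2.12 names program completion as the measure for that objective and defines it as the "percentage of participants that completed the 12‐week program of exercise or usual care, from those that underwent initial randomization". The numerator therefore includes people who complete usual care, and the denominator is everyone randomized. The definition gives one percentage and does not mention a split by arm.

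Section 2.5 plans 24 participants, "12 interventions and 12 usual care controls". Section 2.22 says of the controls that "with the exception of the trial assessments they will not be asked to attend any additional visits or sessions". Retention is a separate objective, Cv in Table 1.

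Section 2.26.1 promises description by trial arm for the mechanistic, physiological and clinical outcomes. It makes no such statement for the feasibility outcomes. Section 2.32 gives a possible progression criterion, still to be finalized: "a minimum of 80% of consented participants randomized to the intervention group engaging with the 12‐week HH4P intervention".

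**The concern.** The measure and its objective concern different groups. Half of the planned denominator is never offered the program whose completion is in question. A control has no exercise program to abandon, so completing usual care amounts to staying in the trial, which Objective Cv already covers. One pooled percentage mixes Aiii with Cv and answers neither cleanly.

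What is at stake is a headline feasibility result. The abstract and the Background give doubtful adherence to extended HIIT programs as a reason for the study, and the abstract names completion among the outcomes. If exercise participants drop out more than controls do, the pooled figure understates the problem, and a reader of the results would take it as a statement about the exercise program.

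**Working it through.** **Inputs.** 24 randomized, 12 per arm (Section 2.5). Numerator and denominator of program completion as defined in Section 2.12. The protocol gives no expected value for program completion and none by arm, so the completer counts below are assumptions, shown over a range.

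**The plan's own related figure.** Section 2.5 expects that "retention rates will be at least 85%, leaving a likely sample at the final follow‐up of between 20 and 24 participants". Check: 0.85 × 24 = 20.4, which rounds to 20, so the stated range reproduces. It is an overall retention figure and says nothing about how losses divide between the arms.

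**Formulas.** Let h be exercise completers and c be control completers, each out of 12.

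- Completion as Objective Aiii words it: h/12.
- Completion as Section 2.12 defines it: (h + c)/24, which with equal arms is the simple mean of h/12 and c/12.

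**Results.**

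| Exercise completers h | h/12 | Pooled, c = 12 | Pooled, c = 11 | Pooled, c = 10 |
|---|---|---|---|---|
| 6 | 50.0% | 75.0% | 70.8% | 66.7% |
| 7 | 58.3% | 79.2% | 75.0% | 70.8% |
| 8 | 66.7% | 83.3% | 79.2% | 75.0% |
| 9 | 75.0% | 87.5% | 83.3% | 79.2% |
| 10 | 83.3% | 91.7% | 87.5% | 83.3% |

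Worked line: h = 8 and c = 12 gives (8 + 12)/24 = 20/24 = 83.3%, against 8/12 = 66.7%.

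**Reading the table.** The gap between the pooled figure and the exercise-arm figure is (c − h)/24. For h = 8 it is 4/24 = 16.7 percentage points with no control lost, 3/24 = 12.5 with one lost, and 2/24 = 8.3 with two lost. The exercise-arm shortfall appears at exactly half its size only when every control completes. If the arms complete equally (h = c = 10) the two figures agree. If controls drop out more, the pooled figure falls below the exercise-arm figure: h = 12 and c = 10 gives 22/24 = 91.7% against 100%.

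**One pooled value, several exercise results.** 20/24 arises from 8 + 12, 9 + 11 or 10 + 10, that is, from exercise-arm completion of 67%, 75% or 83%. The pooled percentage cannot tell these apart.

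**Precision.** Exact (Clopper-Pearson) 95% intervals: 8/12 gives 34.9% to 90.1%; 20/24 gives 62.6% to 95.3%. The pooled interval is narrower, at 32.7 against 55.2 points wide, but it describes a different quantity.

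**The case against.** **The sentence can be read arm by arm**, each participant completing whichever of the two was allocated, and a separate analysis plan may present the figure by arm. That is possible. But the definition states one percentage with all randomized participants as denominator, and the by-arm commitment in Section 2.26.1 covers only the other group of outcomes. Following the text as it stands gives the pooled figure.

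**Controls are not free of demands.** They attend the second assessment visit (Section 2.10) with blood sampling and a maximal exercise test (Section 2.15), wear activity monitors again in week 7 (Section 2.16), know their allocation (Section 2.21) and are asked not to begin additional structured exercise (Section 2.22). This stands. Near-complete control retention is therefore an assumption, and the table varies it. It does not rescue the definition, since those demands belong to trial participation and not to the HH4P program.

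**Exercise-arm behaviour is recorded elsewhere.** Section 2.12 also lists group-session attendance, session frequency and duration, and heart-rate data; Section 2.17 uses diaries and heart rate for fidelity; Section 2.26.1 promises a participant flow diagram. This also stands. A careful reader of a full report could probably see heavy dropout from the exercise program. It limits the harm, but the completion figure would still be wrong for its objective.

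**Two stronger readings are tempting.** A reader might infer that the pooled figure lets a failing program pass the 80% progression threshold, or that Sections 2.12 and 2.32 contradict each other on the denominator. The document supports neither. The Section 2.32 criterion concerns engagement, is already restricted to the intervention arm and is tentative; Section 2.12 attaches no threshold to completion; and two different measures may have different denominators. A reader might also take the 8-of-12 example to mean that a third of all participants dropped out. It is a third of the exercise arm, 4 of 24 overall (17%).

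**Conclusion.** The point holds as a mismatch between a stated definition and the objective it serves. Section 2.12 measures completion across both arms, whereas Objective Aiii asks about the exercise program only. With 12 per arm, 8 exercise completers would be reported as 83% instead of 67% if every control completes, as 79% if one control is lost, and as 75% if two are lost. These sizes rest on assumed completer counts and on the planned equal arms. The direction of the distortion depends on which arm loses more.

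The consequence is confined to the reported completion result and does not reach the progression decision directly. The correction is simple and best made before results are known.

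**What to change.** In Section 2.12, define HH4P program completion for Objective Aiii as the number completing the 12-week exercise program divided by the number randomized to HH4P (planned denominator 12), with an exact 95% confidence interval. Report control-arm retention separately, under Objective Cv.

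The change rewords one definition and needs no extra data. The completion figure may be less favourable, and with a denominator of 12 instead of 24 its interval will be wider, as the two intervals above show.
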